### Baseline data

#### Sociodemographic data

Data on age, gender, self-report ethnicity, occupational status, educational attainment, marital status, literacy and family history of CVD will be collected.

#### Biomedical data

We will collect data on weight, height, BMI, waist circumference, lipids and glycated haemoglobin (HbA1c). We are not measuring fasting glucose as it is not essential to the current diagnosis criteria for diabetes. Weight will be measured in light clothing, without shoes, on a Class 3 Tanita SC240 weighing digital scale (Tanita, Tokyo, Japan) to 0.01 kg for weight and body fat composition. Height will be measured to 0.1 cm using stadiometers (Tantita, Tokyo, Japan) with the supported stretch stature method. Weight and height measurements will be used to calculate BMI (weight/height, kg/m^2^). Waist circumference will be measured horizontally halfway between the lowest rib and the upper prominence of the pelvis using a non-extensible steel tape against the bare abdomen. Blood pressure and resting heart rate will be measured with digital Omron BP monitors (Omron, Kyoto, Japan) using standardised procedures of the average of two readings taken one minute apart while seated. The QRISK2 score will be the research measure of CVD risk.

#### Lifestyle data

We will collect data on smoking status: if current how many cigarettes per day, ex-smoker (for how many years) and never smoked. We will collect and store blood samples for later measurement of cotinine levels. Alcohol intake will be measured using the Alcohol Use Disorders Identification Test [39].

Physical activity will be measured objectively using the ActiGraph GT3X accelerometer (ActiGraph, Florida, United States), a tri-axial movement sensor which also records step counts. The ActiGraph instrument has been validated and will collect data on number of steps taken and physical activity from sedentary to very vigorous [40]. The researcher will explain to the participant how to wear the accelerometer; on a belt over the hip for seven days, from waking in the morning until going to bed at night, and only removing for bathing. Participants are asked to keep a log of activities, including sedentary ones, to assist with the qualitative interpretation of the data. The output from the accelerometer includes number of steps and time spent doing physical activity using standard cut-off points for sedentary, light, moderate, vigorous and very vigorous physical activity. The researcher will ensure that, on the participant returning the accelerometer, it has been worn for at least 540 minutes on each of at least five days, and if not the participant will be asked to wear the accelerometer for another seven days. A measurement of physical activity at moderate level or greater (MVPA) in longer than 10 minute bouts will be extracted from the data collected.

Dietary intake will also be assessed. A standardised multiple-pass 24-hour dietary recall will be carried out as it can be more objective and more reliable as a measure of change in intervention studies. Researchers will be trained to follow a standardised protocol, ask neutral probing questions to encourage recall of food items, and taught about different methods of food preparations and brands in different cultures. Portion size will be assessed with food photographs to estimate daily calorie intake [41,42]. Total and non-HDL cholesterol will be measured as a proxy biomarker of change in dietary fat intake.

#### Psychological data

Health beliefs about diet, exercise and perceptions of risk for developing CVD and related conditions will be measured by the Brief Illness Perception Questionnaire, adapted for perception of risk [43]. Self-report physical activity will be measured by the Global Physical Activity Questionnaire (GPAQ) and International Physical Activity Questionnaire (IPAQ) [44]. Self-efficacy measures for physical activity and dietary habits will be included as psychological processes we are seeking to change during the intervention [45]. Depressive symptoms will be measured using the nine-item Patient Health Questionnaire [46], as depression is associated with worse outcomes in CVD [47].

### Randomisation and allocation concealment

Randomisation of participants will be conducted by the data manager from an independent Clinical Trials Unit (King's College London) using computer-generated randomisation blocks with block sizes of 10. In each block, 10 subjects will be randomised to group, individual or usual care in a 4:3:3 ratio. The unequal allocation ratio ensures that the group arm will have approximately 33% more patients, allowing the group sessions to run with a sufficient number of participants. As this is a complex intervention, it is not possible to conceal the allocation to the participants or the HLFs. Assessors and technicians will be blind to the allocation for the primary and secondary outcomes. There is a small inevitable risk that allocation will be revealed to the outcome assessors, which will be minimised by requesting and reminding participants not to reveal their allocation.

### Planned interventions

#### Group one: usual care

GPs participating in the study will be expected to follow their local Health Check pathway for those who have a CVD risk score of ≥20%.

#### Group two: usual care and enhanced motivational interviewing in a group format

##### Theoretical framework

The intervention will be based on the theory of planned behaviour [28] for initiation of behaviour change, which states that in order to change behaviour, people need to form an intention. Intention formation is influenced by three constructs: expected value or positive attitude (people see the value in making the change); subjective norm (significant others and peers also value the change) and self-efficacy (people believe they are capable of making the change).

Our intervention will tap into all three constructs using principles and techniques from MI [19], CBT [48] and social cognitive theory [49] (Figure 2). MI will be used to support participants in forming healthy intentions. MI is a collaborative conversation style for strengthening a person’s own motivation, belief and commitment to change. Hobbis and Sutton highlight the gap between translating intention into action and illustrate how CBT can be applied to bridge this gap [48]. For this intervention, techniques from CBT will be used to support the transition from intention to action, and action to maintenance [50]. Identifying and challenging unhelpful thoughts or thinking styles can promote more positive emotions and behaviours [51]. For example, ‘When I get breathless after some exercise (bodily sensation) this means I am going to damage my heart (incorrect cognition)’ or ‘I have eaten one doughnut (behaviour) - I might as well eat the whole bag (all or nothing cognition)’.

**Figure 2 Fig2:**
[figure not shown]
**Intervention map of MOVE-IT for cardiovascular disease risk scores of more than 20%.**

Social cognitive theory emphasises the importance of significant others in shaping people’s behaviours. The theory of planned behaviour also highlights this aspect through the ‘subjective norm’ construct. In our intervention, social networks from the participant’s own life and/or group members (in the group arm) will be actively utilised to provide practical and emotional support and opportunities for modeling health behaviours during all phases of the intervention.

##### Intervention development

We will conduct a scoping study to identify manuals published in English in the last five years to improve diet and/or physical activity in the peer-reviewed and grey literature. The aim is to map the quality, contents and cultural diversity of these manuals to inform the content of our intervention. The clinical psychologist will devise the intervention based on this synthesis and on our expertise in developing lifestyle interventions. We will use an iterative process to draft the manual and refine it over two to three cycles. There will be three manual outputs from the trial:A training manual: This will describe the teaching methods, structure and content of the training programme used to train the HLFs.An intervention curriculum: This will describe the outline of each intervention session including key learning points, interactive activities and action planning.A participant workbook: This will include key learning points from each session, action planning worksheets, case studies and a self-monitoring diary for each participant. The participants will also receive a pedometer with guidance on how to use this effectively and access to online, DVD and paper resources around CVD risk.

The programme will consist of 10 sessions, plus an introductory session, spread quarterly over 12 months. The outline of each session is described in Table 1. Each participant allocated to a treatment arm will have a session 0 as an introduction to the intervention, to receive their intervention packs and to become familiar with the HLF. The intensive phase consists of six weekly sessions at the beginning of the first quarter. The first three sessions focus on physical activity and the second three sessions focus on diet. The maintenance phase consists of four sessions delivered at three, six, nine and twelve months. Those randomised to the group arm are encouraged to use the peer learning and peer support environment to facilitate change during the intensive phase and maintenance phase. Each group has typically 10 to 11 participants and sessions last 120 minutes. The intervention will be delivered in local venues such as community halls and health centres. In between sessions and during the follow-up period, participants will be encouraged to communicate with each other (in the group arm) and the HLF (both individual and group). Novel methods and teaching aides are used to supplement the delivery of behaviour change techniques such as visual aids of food labels and/or cue cards, exercise demonstrations, video and/or audio material of patient testimonials, activity-based learning around meal planning and text and/or email reminders. For ease of translation, the key components of the programme have been defined according to Abraham and Michie’s behaviour change technique taxonomy [30]:

**Table 1 Tab1:** **Proposed programme of sessions**

**Session number**	**Content of session**
	Intensive phase:
Session 0	Focus: Introduce the intervention
	Examples of delivery: structure of the programme, ice breaker, rapport building with HLF, give out pedometers and baseline measures.
Session 1: physical activity	Focus: Increasing routine activity
(Week 1)	Examples of delivery: Elicit views regarding walking more and sitting less and instruction on use of pedometer. Support individual goal setting.
Session 2: physical activity	Focus: Increasing non routine activity
(Week 2)	Examples of delivery: Elicit views on recommended activity levels and reflect on previously enjoyed exercise and its benefits. Provide information/demonstration/leaflets regarding local exercise options. Support individual goal setting.
Session 3: physical activity	Focus: To maintain physical activity changes
(Week 3)	Examples of delivery: Elicit views regarding lapse versus relapse using case studies. Discuss lapse triggers and strategies to manage them. Support individual relapse prevention plans (including implementation intentions).
Session 4: diet	Focus: Increasing health food choices
(Week 4)	Examples of delivery: Elicit views on healthy eating principles. Interactive games regarding healthy snacks. Support individual goal setting.
Session 5: diet	Focus: Decreasing unhealthy food choices
(Week 5)	Elicit views on foods to avoid in excess. Interactive games regarding food labelling and high fat and salt foods. Support individual goal setting.
Session 6: diet	Focus: To maintain dietary changes
(Week 6)	Examples of delivery: Elicit views regarding lapse versus relapse using case studies. Discuss lapse triggers and strategies to manage them. Support individual relapse prevention plans (including implementation intentions).
	Maintenance phase:
Session 7	Focus: Review progress and problem-solve setbacks
(3 months)	Examples of delivery: Highlight positive changes in review session, discuss setbacks and potential ways forward. Support individual relapse prevention plans.
Session 8	Focus: Review progress and problem-solve setbacks
(6 months)	Examples of delivery: Highlight positive changes in review session, discuss setbacks and potential ways forward. Support individual relapse prevention plans.
Session 9	Focus: Review progress and problem-solve setbacks
(9 months)	Examples of delivery: Highlight positive changes in review session, discuss setbacks and potential ways forward. Support individual relapse prevention plans.
Session 10	Focus: Review progress and problem-solve setbacks
(12 months)	Examples of delivery: Highlight positive changes in review session, discuss setbacks and potential ways forward. Support individual relapse prevention plans.

Provide information on consequences,Prompt intention formation,Prompt barrier identification,Prompt specific goal setting,Prompt review of behavioural goals,Prompt self-monitoring of behavior,Teach to use prompts or cues,Agree on behavioural contract,Use follow-up prompts, Plan social support or social change, Relapse prevention and Motivational interviewing.

##### Training the healthy lifestyle facilitators

The HLFs are at NHS Band 3 level, employed by King's College Hospital and seconded as appropriate to the CCG. The training programme lasts eight weeks. The teaching is a combination of didactic learning, role plays and feedback, group exercises, reading and case study discussion. The HLFs will use rating scales for self-monitoring of skill progression during role plays. The HLF is deemed ready to administer the intervention when they have achieved a specific competency level [52]. We will adapt existing competency frameworks for behaviour change techniques to this study [53-55]. HLFs are expected to offer sessions between 8 am and 9 pm, enabling flexibility for participants who are in full-time work or have carer roles. Cultural and religious awareness is built in. Regular supervision during the intervention will be provided by the clinical psychologist.

#### Group three: usual care and enhanced motivational interviewing in an individual format

This will have the same components as group two but the components are delivered individually. There will be no opportunity, expectation or guidance for participants to form groups with each other in between sessions. Sessions will last 40 minutes. We have kept the number of sessions the same and reduced the duration of each session to approximately match for attention in the two groups.

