#### Secondary hypotheses

Enhanced MI delivered in a group format is more effective than in an individual format in reducing weight and increasing physical activity (average number of steps per day assessed via accelerometry) 24 months later.Enhanced MI, delivered in a group or individual format, is more effective than usual care in reducing LDL cholesterol, reducing CVD risk score and increasing moderate to vigorous physical activity ((MVPA) amount of at least moderate physical activity in longer than 10 minute bouts) 24 months later.Enhanced MI, delivered in a group or individual format, is more cost-effective than usual care, in terms of quality-adjusted life years (QALYs) gained over the 24 month follow-up period.

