## Discussion

This study will compare the effectiveness of enhanced MI interventions, in a group and individual format, with usual care for reducing weight and increasing physical activity in 40 to 74-year-olds with a high risk (≥20%) of developing CVD in the next 10 years. The study will take place across 11 CCGs in South London and will assess changes at 24 months, with an interim assessment at 12 months. The relative effectiveness of group and individual interventions will be assessed; it is predicted that participants in the group intervention will benefit from social support and that this approach will be more cost-effective than the individual format.

The benefits of the study setting include the infrastructure for dissemination of research findings (through the HIN), and that a significant proportion of the South London population is African, Caribbean or South Asian. A limitation is that health inequalities between the north and south of the United Kingdom will not be addressed. However, health inequalities within South London mirror the rest of the United Kingdom, and South London is well-placed in being a geographical setting with a multi-ethnic population across a variably deprived setting, allowing ethnicity and deprivation to be addressed in the study design. Changes in NHS organisation during the course of the study also present challenges, including the transfer of public health responsibilities from the NHS to local government and the change from primary care trusts to CCGs. Poor uptake of the NHS Health Check programme has also prompted changes to recruitment procedures. Variably outdated data on patient records systems may lead to inaccurate estimate of CVD risk and, therefore, large numbers of ineligible participants consented.

The intervention offers the advantage of potentially active ingredients to support maintenance, such as social support within the group intervention and a long-term follow-up period. One challenge is in avoiding selection bias in the study design and ensuring the intervention targets those most at need, as participants who respond to the invite to take part in the study may already be motivated. However, as the participants will have screened at high risk of CVD there is cause for treatment.

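### The session figures do not bear out the claim that the group and individual formats are approximately matched for attention, so their contrast cannot isolate social support

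*Protocol article*

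**What the plan says.** Intervention development sets out the programme: "The programme will consist of 10 sessions, plus an introductory session, spread quarterly over 12 months". For the group arm it adds: "Each group has typically 10 to 11 participants and sessions last 120 minutes".

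The section on group three (individual format) describes the other active arm: "This will have the same components as group two but the components are delivered individually". On length it says: "Sessions will last 40 minutes". It then gives the reason: the authors left the session count unchanged and "reduced the duration of each session to approximately match for attention in the two groups". Attention is not defined, and no figure is given for the match.

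The contrast between the two formats is the first of the Secondary hypotheses: "Enhanced MI delivered in a group format is more effective than in an individual format in reducing weight and increasing physical activity". The Sample size section also lists it among the three contrasts that justify a two-tailed alpha of 0.025. The Discussion names the expected mechanism: "it is predicted that participants in the group intervention will benefit from social support". The Abstract and the Summary at the end of the Background likewise present social support as what the group format adds.

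**The concern.** Attention can be counted as the time a participant spends in sessions, or as the facilitator time available to each participant. If the arms were close on one of these, a difference between them could not easily be put down to that measure. The stated session lengths and group size suggest that they are close on neither.

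What is at stake is the interpretation of the secondary contrast. The matching sentence is the only design feature offered that would support reading a difference as the work of peer support. Without it, a group advantage could come from longer contact. An individual advantage, or no difference, could reflect the larger facilitator share in that arm.

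**Working it through.** **Inputs**
- Sessions: 10, plus session 0, the same number in both formats (Intervention development; group three section).
- Session length: 120 minutes for group, 40 minutes for individual (same two sections).
- Group size: 10 to 11 (Intervention development).
- Facilitators per group: not given. One is assumed, and two are shown as a variant.
- Length of session 0: not given separately. Where it is included, it is assumed to have its format's usual length.

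**The plan's own figure.** The match is stated in words only. A match would mean a ratio near 1 on some measure of attention.

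**Measure A: scheduled contact per participant** = sessions × minutes per session.
- 10 sessions: group 10 × 120 = 1,200 minutes (20 h); individual 10 × 40 = 400 minutes (6.7 h). Ratio 1,200/400 = 3.0.
- With session 0: 11 × 120 = 1,320 minutes; 11 × 40 = 440 minutes. Ratio 3.0.

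**Measure B: facilitator time per participant per session** = minutes × facilitators / participants present.

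| Group session | Minutes per group participant | Individual (40 min) / group |
|---|---|---|
| 1 facilitator, 10 present | 120/10 = 12.0 | 3.3 |
| 1 facilitator, 11 present | 120/11 = 10.9 | 3.7 |
| 2 facilitators, 10 present | 240/10 = 24.0 | 1.7 |
| 2 facilitators, 11 present | 240/11 = 21.8 | 1.8 |

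Over 10 sessions with one facilitator, this is 109 to 120 minutes in the group arm against 400 in the individual arm.

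**Sensitivity to attendance** (assumed range, one facilitator, group of 10 or 11). At 75% attendance the individual arm has 2.5 to 2.75 times the facilitator time per participant. At 50% it has 1.7 to 1.8 times. Parity at these session lengths would need 120/40 = 3 people in the room.

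The ratio does not come near 1 on either measure, and the two gaps run in opposite directions. Contact between sessions, which the protocol encourages with the facilitator in both arms and among peers in the group arm only, is not counted because no amount is given.

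**The case against.** The best defence is that the wording is approximate and attention is undefined. No group larger than one can match a one-to-one session on both measures: at these figures, equal contact would mean 120 minutes and equal facilitator share 11 to 12. The geometric midpoint is 120/√10.5 ≈ 37 minutes, close to the stated 40, so the length is compatible with a compromise, and the number of sessions is matched. This is fair as far as it goes, and it is a reason not to call the two sections flatly contradictory: they describe different arms, and only the matching clause is in question. But the protocol does not state such a compromise, and a midpoint that misses about threefold each way is not a match on either measure.

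A reader might go further and infer that the contrast cannot be read as an effect of format at all. The document does not support that. Allocation is randomised, and the secondary hypothesis asks only whether one format works better than the other. Session length, shared facilitator time and peer contact are parts of each format as defined, so they do not confound the comparison of the formats as delivered.

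A reader might also infer that this undermines a contrast the trial was powered for. The Sample size section ties its 1,420 participants to the primary hypotheses and lists group versus individual in justifying the alpha; the contrast itself is a secondary hypothesis.

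Finally, the social-support statement is a prediction in the Discussion, and the statistical analysis section does not commit to that attribution. This limits the stakes, but the prediction still needs a qualification.

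**Conclusion.** The point holds in a limited form. The attention-matching clause is not borne out by the session figures. The 3:1 gap in scheduled contact, in favour of the group arm, follows directly from the stated lengths and needs no staffing assumption. The gap in facilitator time, in favour of the individual arm, is 3.3 to 3.7:1 at full attendance with one facilitator per group. It shrinks to about 1.7 to 1.8:1 with two facilitators at full attendance, or with one at an assumed 50% attendance.

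The group versus individual contrast remains a valid randomised estimate of the effect of offering one package rather than the other. It cannot separate social support from contact time and facilitator share, and it does not estimate the effect of format at equal attention. The primary comparisons of each format with usual care do not rely on the matching. No sample size, alpha or model is affected.

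**What to change.** 1. In the group three section, delete the attention-matching clause, or name the measure meant and reconcile it with the session lengths and group size given there and in Intervention development. No session length is proposed here.
2. State that group versus individual compares two delivery packages that differ in contact time, facilitator share and peer contact.
3. Report delivered contact minutes and session attendance by arm, with the number of facilitators per group session.
4. Qualify the social-support prediction in the Discussion: a difference between the formats would be consistent with that mechanism but would not isolate it.

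The cost is a few sentences and one descriptive table. The extra data burden should be small, because the economic evaluation already apportions group costs over attendees and so needs attendance records. The price is a narrower secondary conclusion: the trial can say which package did better, but not why.
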